### Samples collection and healthy control recruitment

2.8

For the analysis of fecal microbiota and related metabolites, blood, urine, and stool samples are collected before and after treatment and will be analyzed under standardized laboratory testing process. In addition to the IBS-C participants, 30 healthy volunteers aged 21 to 65 years (inclusive) are recruited from the general population through flyers and online platforms. These individuals must not have any diagnosed gastrointestinal disorders, chronic diseases, or recent use of antibiotics or probiotics. The healthy control group serves as a baseline reference for microbiota composition and metabolite levels, helping to distinguish disease-specific features in IBS-C patients and access changes induced by EA. These volunteers do not receive any interventions and are included only for observational comparison.

### Statistical analyses

2.9

All efficacy and safety analyses will be conducted based on intention-to-treat (ITT) principle. Missing values will be imputed by the last-observation-carried-forward method. Statistical analysis will be performed using the Stata software, with statistical significance defined as a two-sided *p*-value of <0.05. Baseline characteristics will be reported as mean (SD). Baseline differences between the groups will be evaluated using Student’s t-test for normally distributed continuous variables and the non-parametric Mann–Whitney U test for non-normally distributed variables. For categorical variables, the chi-squared test or Fisher’s exact test will be applied. Comparisons between groups will be conducted by using the unpaired t-test for normally distributed data and the Mann–Whitney test for non-normally distributed data. Within-group differences will be evaluated using the paired t-test for normally distributed data and the Wilcoxon signed-rank test for non-normally distributed data.

To minimize the risk of false positives, multiple-testing correction methods will be applied during the data analysis process where appropriate. Additionally, advanced statistical methods, including the Logistic Generalized Linear Mixed Model (GLMM), will be applied. Potential inter-center differences in study outcomes will also be assessed.

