### Study design

2.1

This pilot, randomized, double-blinded, sham-controlled trial is being conducted in Singapore since September 2024 (with the first patient enrolled). The study design strictly adheres to the principles of Declaration of Helsinki, Good Clinical Practice (GCP) guidelines, and mirrors STandards for Reporting Interventions in Clinical Trials of Acupuncture (STRICTA) guideline and the Consolidated Standards of Reporting Trials (CONSORT) statement, including the CONSORT-Outcomes 2022 extension (21, 22). The study lasts for a total of 14 weeks. All eligible patients first undergo a 2-week screening period, which includes providing blood samples for routine testing prior to enrollment. After the screening period, eligible patients are randomized in a 1:1 ratio to receive either EA or sham acupuncture over a 6-week intervention period, followed by a 6-week follow-up phase (Figure 1; Table 1). Sham acupuncture is selected as to offset the placebo effect of acupuncture, and there is no standard medication in treating IBS-C.

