### Outcomes and data collection

2.4

Daily symptoms recorded in physical or online patient diary include the number of BMs, SBMs, CSBMs, along with the severity of abdominal pain, discomfort, straining, and bloating, assessed using an 11-point scale (0 = none, 10 = worst possible). For each BM, stool consistency (7-point Bristol Stool Form Scale), sensation of severe straining during defecation, and use of medication are also recorded. Data will be entered electronically and stored in an encoded database within 24 h of receipt, with double data entry and range checks. Access to the trial dataset is restricted to investigators.

The primary outcome of the study is defined as responders who have a decrease in the weekly average of worst abdominal pain scores of ≥30% compared with baseline and a weekly increase of ≥1 CSBM from baseline (24). To assess the response over time, data between 2 groups will be summarized and compared throughout the treatment period and at the end of follow-up.

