### Sample size calculation

2.5

Our study is the first sham-controlled acupuncture trial that uses the Food and Drug Administration (FDA) recommended end point for IBS-C. The sample size was determined based on the study’s objectives, statistical precision, feasibility, and previously reported clinical response rates in IBS-C acupuncture trials. We referenced a randomized controlled trial by Pei et al. (28), which reported a significant difference in clinical effective rates between the acupuncture and control group. Assuming a two-sided alpha of 0.05, power of 80%, an expected response rate of approximately 70% in the acupuncture group versus 30% in the sham control group, and accounting for a 20% dropout rate and potential missing data, a total sample size of 60 patients (30 in the experimental arm and 30 in the control arm) was designed to detect clinically meaningful differences.

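### Last-observation-carried-forward is the only stated rule for missing data; it can bias the comparison in either direction and overstates durability if the electro-acupuncture effect wanes more than sham

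*Protocol article*

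**What the plan says.** Section 2.9 (Statistical analyses) opens with "All efficacy and safety analyses will be conducted based on intention-to-treat (ITT) principle" and continues: "Missing values will be imputed by the last-observation-carried-forward method". No outcome, visit or type of missingness is singled out. The same section promises advanced methods, "including the Logistic Generalized Linear Mixed Model (GLMM), will be applied", but does not connect that model to the primary endpoint or to missing data.

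Section 2.4 (Outcomes and data collection) defines the primary outcome as a responder status with two weekly parts: a "decrease in the weekly average of worst abdominal pain scores of ≥30% compared with baseline" and "a weekly increase of ≥1 CSBM from baseline". It adds that "data between 2 groups will be summarized and compared throughout the treatment period and at the end of follow-up". Section 2.1 describes treatment "over a 6-week intervention period, followed by a 6-week follow-up phase". The text below Table 1 requires daily diaries until the trial ends, whereas Table 1 schedules the questionnaires at weeks 0, 4, 7 and 13.

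Section 2.5 plans 60 patients, 30 per arm, at 70% versus 30% response, two-sided alpha 0.05 and 80% power, "accounting for a 20% dropout rate and potential missing data".

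**The concern.** This is a method the article fixes, not a detail left to an analysis plan. Followed as written, a patient who meets the weekly definition once, in treatment week 3, and then leaves is scored a responder in treatment weeks 4 to 6 and again at the end of follow-up. One observed response stands in for three further treatment weeks and for the follow-up result.

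Three things are at stake:

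- **The responder comparison.** Its value would depend partly on what leavers reported just before they left, with 20% of patients expected to leave.
- **Precision.** Carried values enter the tests as if they had been measured.
- **Durability.** The follow-up phase asks whether the effect lasts. A rule that extends an earlier status into that phase presumes part of the answer.

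**Working it through.** **1. The plan's own figure.** Inputs from section 2.5: 70% versus 30%, two-sided alpha 0.05, power 80%, dropout 20%. With pooled variance and no continuity correction:

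n = [1.96·√(2·0.5·0.5) + 0.842·√(0.7·0.3 + 0.3·0.7)]² / 0.40² ≈ 23.3, so 24 per arm.

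24 / (1 − 0.20) = 30 per arm, 60 in total. The stated size reproduces. It treats the 20% who leave as contributing no information, whereas LOCF analyses them as fully observed.

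**2. End of treatment.** Let d be the dropout share, p the completer response rate and r the share of leavers responding at their last observation. The rates p = 70% and 30% are the planning rates; r, and any split of dropout by arm, are assumptions.

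- LOCF rate = (1 − d)·p + d·r
- Leavers counted as non-responders = (1 − d)·p

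| Dropout EA / sham | r EA / sham | LOCF difference | Non-responder difference |
|---|---|---|---|
| 20% / 20% | 70% / 30% | 0.70 − 0.30 = 0.40 | 0.56 − 0.24 = 0.32 |
| 20% / 20% | 100% / 0% | 0.76 − 0.24 = 0.52 | 0.32 |
| 20% / 20% | 50% / 50% | 0.66 − 0.34 = 0.32 | 0.32 |
| 20% / 20% | 20% / 50% | 0.60 − 0.34 = 0.26 | 0.32 |
| 30% / 10% | 70% / 30% | 0.40 | 0.49 − 0.27 = 0.22 |
| 10% / 30% | 70% / 30% | 0.40 | 0.63 − 0.21 = 0.42 |

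The two rules can differ widely, and the LOCF difference can be the larger, the same or the smaller. At 30 per arm, power is 89.3% for 70% versus 30% and 72.7% for 56% versus 24%.

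**3. Precision.** At the planning rates, the standard error of the difference is √(0.42/24) = 0.132 with the 24 per arm expected to be observed, and √(0.42/30) = 0.118 if all 30 are treated as observed. The smaller figure is earned only if the carried statuses are true.

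**4. End of follow-up.** Let m be the share missing at week 13, e the end-of-treatment rate (70% EA, 30% sham) and f the true rate at week 13. Missingness is assumed unrelated to status, and the carried value is assumed to be the end-of-treatment one.

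LOCF rate = (1 − m)·f + m·e

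| True EA / sham | m | LOCF EA / sham | LOCF difference | True difference |
|---|---|---|---|---|
| 30% / 30% | 10% | 34% / 30% | 4 points | 0 |
| 30% / 30% | 20% | 0.8·0.30 + 0.2·0.70 = 38% / 30% | 8 points | 0 |
| 30% / 30% | 30% | 42% / 30% | 12 points | 0 |
| 40% / 30% | 20% | 46% / 30% | 16 points | 10 points |
| 50% / 30% | 20% | 54% / 30% | 24 points | 20 points |
| 50% / 10% | 20% | 54% / 14% | 40 points | 40 points |
| 80% / 30% | 20% | 78% / 30% | 48 points | 50 points |

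The difference is overstated when EA wanes more than sham. It is unbiased when both fall equally, although each arm's rate is then 4 points too high. It is understated when EA goes on improving.

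**The case against.** A reader might infer that LOCF is bound to favour EA, and quote 40 points against 32 as its inflation. The documents do not support that. They give neither dropout by arm, nor leavers' last status, nor the course after treatment. If leavers keep the status they left with, 40 points is the truth and counting them as failures understates it. The 8-point gap is a difference between two conventions, about 2.4 patients net at 30 per arm (0.08 × 30). Patients who leave for lack of benefit carry non-response forward, and a patient with no post-baseline diary carries baseline and also counts as a non-responder. This objection stands, so no direction is claimed for the end-of-treatment contrast.

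The follow-up example is also conditional. Diaries run to the end of the trial, so the carried value for the diary-based primary outcome may come from a follow-up week. The example fits questionnaires better: a patient lost between weeks 7 and 13 has the end-of-treatment score reported as the follow-up result.

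Two further inferences go too far. One is that adverse events will be imputed: section 2.9 speaks only of missing values, and section 2.7 bases safety on documented events. The other is that the damage cannot be undone after unblinding: LOCF deletes no observed data, so other analyses remain possible, though less credible if chosen then.

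Finally, the trial calls itself a pilot and asks for cautious interpretation. It nevertheless has an efficacy primary outcome and a power calculation, so the handling of missing data matters. A separate analysis plan might add sensitivity analyses; their absence from the article is not the point here.

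**Conclusion.** The concern holds as a criticism of a stated method. LOCF is the only rule given, it is unrestricted, and 20% dropout is planned. It can move the EA–sham contrast either way and can overstate precision. In the scenarios above with 20% dropout in each arm, the LOCF difference at end of treatment ranges from 0.26 to 0.52 according to leavers' last status, which the trial cannot know in advance.

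It overstates durability only if the EA effect wanes more than sham. In that case, with 20% missing and end-of-treatment status carried, a vanished effect would still show 8 points (4 to 12 points for 10% to 30% missing). These sizes rest on the planning rates of 70% and 30%, a sham rate that stays at 30%, and missingness unrelated to status.

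**What to change.** Change the rule before unblinding. Section 2.6 keeps the study blinded until the final analysis, so on the text shown this is still possible.

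- **Responder endpoint:** count a week without evaluable diary data as non-response, so that an early response is not credited to later weeks. Add a multiple-imputation or tipping-point sensitivity analysis, because non-responder imputation is itself a convention and can mislead when dropout differs by arm. With a true 40% in both arms and dropout of 30% EA and 10% sham, it gives 0.7·0.40 = 28% versus 0.9·0.40 = 36%.
- **Repeated continuous and scale outcomes:** use a likelihood-based mixed model on the observed data with baseline included, or multiple imputation.
- **LOCF:** keep it at most as a labelled sensitivity analysis.

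The cost is revised analysis wording, a little more programming and, for a protocol amendment, the ethics review that section 2.10 requires. The downside is that responder rates and power look less favourable: at the planning rates with 20% dropout counted as failures, 56% versus 24% and about 73% power at 30 per arm, against the 80% stated.

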Other measurements include: (1) Proportion of patients with an improvement of ≥30% in abdominal pain scores from baseline; (2) Proportion of patients with an average increase of 1 or more CSBMs per week as compared with the baseline; (3) Average number of SBMs, CSBMs per week; (4) Percentage of bowel movements with normal consistency; (5) Percentage of bowel movements with severe or very severe straining during defecation; (6) Median time to the first SBMs, CSBMs after first session of EA; (7) Average number of bisacodyl tablets or enemas used per week; (8) Global assessment of efficacy of treatment with Likert scale at mid-treatment, end of the treatment, and end of follow-up; (9) IBS-C related severity and quality of life scores such as IBS Symptom Severity Scale (IBS-SSS), IBS Quality of Life (IBS-QOL), Patient Assessment of Constipation Symptoms (PAC-SYM), Constipation Quality of Life (PAC-QOL) and Patient Health Questionnaire-15 (PHQ-15) at the start of the treatment, mid-treatment, end of the treatment, and end of follow-up; (10) Depression, anxiety, and stress symptoms in IBS-C patients by Hamilton Depression Scale (HAMD), Self-rating Depression Scale (SDS), Patient Health Questionnaire (PHQ-9), General Anxiety Disorder (GAD-7), Hospital Anxiety and Depression Scale (HADS), Visceral Sensitivity Index (VSI) and Perceived Stress Scale (PSS) at the start of treatment, end of treatment, and end of follow-up; (11) Patient expectancy and trust in treatment, assessed via a brief questionnaire at the start of treatment, end of treatment, and end of follow-up; (12) Feasibility outcomes, including recruitment and retention rates, adherence to treatment protocols, completeness and quality of symptom diaries and questionnaire responses, and documentation of adverse events throughout the study. In addition to the primary and secondary outcomes, dietary intake and TCM constitutional patterns are assessed using the Food Frequency Questionnaire (FFQ) and Short-Form Wang Qi’s Body Constitution Classification Questionnaire (SF-CCMQ).

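### Continuous secondary outcomes with a recorded baseline are compared by unadjusted tests chosen on normality; adjusting for that baseline would be more precise and needs no new data

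*Protocol article*

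**What the plan says.** Section 2.9 (Statistical analyses) gives the rule for comparing arms: "Comparisons between groups will be conducted by using the unpaired t-test for normally distributed data", and the Mann-Whitney test for data that are not normal. No covariate is named, and the quantity compared (post-treatment value or change) is not stated. The same section plans tests of baseline balance ("Baseline differences between the groups will be evaluated using" t, Mann-Whitney, chi-squared or Fisher tests). The only model it names is a logistic mixed model, without an outcome or covariates. On centre it says: "Potential inter-center differences in study outcomes will also be assessed".

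Baseline values are collected. Section 2.1 has patients keep the daily diary from the start of the two-week screening period. Section 2.4 schedules IBS-SSS, IBS-QOL, PAC-SYM, PAC-QOL and PHQ-15 "at the start of the treatment, mid-treatment, end of the treatment, and end of follow-up". The mood and stress scales are taken at the start of treatment, at its end and at the end of follow-up.

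**The concern.** When an outcome is also measured before treatment, part of its between-patient variation can be predicted from that earlier value. A two-sample test leaves this variation in the error term; a model with baseline as covariate removes it. With about 30 patients per arm, the difference in precision can be material.

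The unstated choice between post-treatment values and changes also matters. Write D for the chance difference between arms at baseline and r for the baseline-outcome correlation, with equal SDs at the two times. A comparison of post-treatment values is shifted by rD, and a comparison of changes by −(1−r)D. ANCOVA removes the shift in both cases.

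Finally, letting the normality of the data pick the test means that related scales may be reported on different footings, a difference in means for one and a rank comparison for another. That is awkward for a pilot meant to inform larger trials.

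**Working it through.** **The plan's own figure.** Section 2.5 assumes two-sided alpha 0.05, 80% power, "an expected response rate of approximately 70% in the acupuncture group versus 30% in the sham control group", and a total of 60 after "accounting for a 20% dropout rate and potential missing data". With the pooled-variance formula:

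n per arm = [1.96 × √(2 × 0.5 × 0.5) + 0.8416 × √(0.7 × 0.3 + 0.3 × 0.7)]² / 0.4² = (1.386 + 0.545)² / 0.16 ≈ 23.3, rounded up to 24.

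24 / 0.8 = 30 per arm, 60 in total. The figure reproduces. It rests on a binary responder outcome, so nothing below alters it.

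**Inputs for the continuous outcomes.** 30 per arm as randomised, or 24 per arm if 20% drop out (section 2.5). The correlation r is not in the article and is assumed at 0.3, 0.5 and 0.7. SDs are taken as equal at baseline and follow-up.

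**Variance of the estimated difference**, in units of the post-score t-test:
- t-test on post-treatment scores: 1
- t-test on change scores: 2 − 2r
- ANCOVA: 1 − r²
- ANCOVA relative to change scores: (1 − r²)/(2 − 2r) = (1 + r)/2

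| r | ANCOVA vs post | 60 patients act like | ANCOVA vs change | 60 patients act like |
|---|---|---|---|---|
| 0.3 | 0.91 | 60/0.91 ≈ 66 | 0.65 | 60/0.65 ≈ 92 |
| 0.5 | 0.75 | 60/0.75 = 80 | 0.75 | 60/0.75 = 80 |
| 0.7 | 0.51 | 60/0.51 ≈ 118 | 0.85 | 60/0.85 ≈ 71 |

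The reduction is thus 9% to 49% against post scores and 15% to 35% against change scores.

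**Smallest difference detectable with 80% power**, in SD units: √(2/n) × (1.96 + 0.8416), multiplied by √(1 − r²) for ANCOVA.

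| n per arm | Post-score t-test | ANCOVA, r = 0.3 | r = 0.5 | r = 0.7 |
|---|---|---|---|---|
| 30 | 0.72 | 0.69 | 0.63 | 0.52 |
| 24 | 0.81 | 0.77 | 0.70 | 0.58 |

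**Power for an illustrative true difference of 0.7 SD, 30 per arm.** The post-score t-test has 77%. For r = 0.3, 0.5 and 0.7, the change-score t-test has 63%, 77% and 94%, and ANCOVA has 81%, 88% and 97%.

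**Simulation check**, with normal data and 4,000 runs per setting. At 30 per arm and 0.7 SD, the post-score t-test had power of 75% to 76%. For r = 0.3, 0.5 and 0.7, change scores gave 62%, 76% and 93%, and ANCOVA 79%, 86% and 96%. The ordering is the same as in the formulas. With no true difference, rejection rates at 24 and 30 per arm lay between 0.045 and 0.055 for every method, including a t-test or Mann-Whitney test picked by a normality pre-test.

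**The case against.** Several stronger readings are tempting, and the article does not support them.

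- *That the plan ignores baseline apart from testing balance.* It does not. The primary outcome is defined by change from baseline in pain and CSBMs, and so are the first two secondary responder outcomes. Section 2.9 also plans paired within-group tests.
- *That the trial as a whole loses the equivalent of some 20 patients.* The primary outcome is binary and the sample size was set on it. The loss concerns secondary outcomes only.
- *That every continuous outcome should have a baseline covariate.* Time to first SBM or CSBM and the global efficacy rating have no baseline.
- *That choosing the test by normality inflates false positives.* The simulation shows no such effect for normal data. Skewed data were not examined.
- *That clinic is mishandled.* Treatment is given at two clinics, and inter-centre differences are to be examined. Whether clinic enters the treatment comparison is commonly settled in the analysis plan, and any gain from it cannot be calculated here.

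Two further objections stand in part. The gain depends on an assumed correlation. Entry limits on pain and CSBMs may lower that correlation for the diary outcomes, and at r = 0.3 the saving against post scores is only 9%. The figures also compare ANCOVA with t-tests, not with Mann-Whitney tests.

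The most serious objection is that an unseen analysis plan, or the open-ended reference to advanced methods, may already supply an adjusted model. Details such as visit structure may well sit there. But the article does not leave the comparison open: it names tests that cannot adjust, and the one model it names suits binary outcomes.

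**Conclusion.** The point holds as one of efficiency and clear specification, not of validity. For the continuous secondary outcomes with a recorded baseline, the stated tests are less precise than a baseline-adjusted analysis, and the compared quantity is not fixed. Over assumed correlations of 0.3 to 0.7, ANCOVA was more precise than either t-test at every value, but the size of the gain runs from modest to large and cannot be narrowed from the article. The calculation assumes a linear relation and equal SDs at baseline and follow-up.

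**What to change.** For weekly SBM and CSBM counts, IBS-SSS, IBS-QOL, PAC-SYM, PAC-QOL, PHQ-15 and the mood and stress scales, replace the normality-selected test with one prespecified model per outcome. This can be ANCOVA at a named time point, or a repeated-measures mixed model with arm-by-visit terms, in either case with the baseline value as covariate. Report the adjusted difference with its 95% confidence interval. Where residuals are skewed, robust or bootstrap standard errors are one option that keeps the same estimand. Treating clinic may be added as a covariate.

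Leave time to first SBM or CSBM and the global efficacy rating outside this change. Dropping the baseline significance tests is an optional reporting improvement: under randomisation they do not correct imbalance.

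The cost is a few lines in the analysis plan and routine Stata code, with no new data or patients. Section 2.6 keeps the study blinded until the final analysis, so the change can still be prespecified if it is made before then.

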**Figure 1 fig1:**
[figure not shown]
Study flow.

**Table 1 tab1:** Schedule of study procedures.

Week	0	2	3	4	5	6	7	13
Visit	1	2–3	4–5	6–7	8–9	10–11	12–14	15
Eligibility assessment	✓	✓						
Informed consent	✓							
Baseline data collection	✓							
Concomitant drug record	✓	✓	✓	✓	✓	✓	✓	✓
Adverse effects assessment		✓	✓	✓	✓	✓	✓	✓
Physical examination and samples collection	✓	✓					✓	
Food frequency questionnaire (FFQ)	✓							
Short-form Wang Qi’s body constitution classification questionnaire (SF-CCMQ)	✓			✓			✓	✓
Questionnaires with psychiatric assessment	✓			✓			✓	✓
Intervention		✓	✓	✓	✓	✓	✓	

Patients are required to fill in their diaries daily from the start of the 2-week screening period until the end of the trial, recording the timing of bowel movements (BMs), stool consistency, degree of straining during defecation, sensation of complete or incomplete evacuation, and the name and dosage of any medications taken. Throughout the trial, patients are asked to avoid making significant lifestyle changes, such as initiating a new diet or modifying their exercise routine. Patients must discontinue any medications listed in the exclusion criteria before entering the trial. Concomitant medications that may affect IBS symptoms, such as antibiotics, antidepressants, probiotics, or herbal medicine, are prohibited for at least 1 month before the screening period. If a participant meets the inclusion criteria but needs to use medications due to a comorbid illness or changes in health status, it will be recorded in the case report form (CRF).

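### Continuous secondary outcomes are compared between arms without baseline adjustment, by a test that the data's distribution picks; a baseline-adjusted model would be more precise at almost no cost

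*Protocol article*

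**What the plan says.** Section 2.9 (Statistical analyses) gives one between-arm rule for continuous data: "Comparisons between groups will be conducted by using the unpaired t-test for normally distributed data". The same sentence names the Mann–Whitney test for data that are not normally distributed. No covariate appears in the rule, and it does not say whether the tested quantity is the value at a visit or the change from baseline.

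Baseline enters section 2.9 in two other ways. The arms are tested for baseline imbalance ("Baseline differences between the groups will be evaluated using Student’s t-test for normally distributed continuous variables", with a rank test otherwise), and each arm is compared with its own baseline ("Within-group differences will be evaluated using the paired t-test for normally distributed data", again with a rank alternative). The section then adds: "Additionally, advanced statistical methods, including the Logistic Generalized Linear Mixed Model (GLMM), will be applied". No outcome, covariate or baseline term is given for that model.

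The pre-treatment values exist:

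- Section 2.1, below Table 1: "Patients are required to fill in their diaries daily from the start of the 2-week screening period until the end of the trial". This supplies screening values for SBM and CSBM counts.
- Section 2.4, item 9, takes the IBS severity and quality-of-life scales (IBS-SSS, IBS-QOL, PAC-SYM, PAC-QOL, PHQ-15) "at the start of the treatment, mid-treatment, end of the treatment, and end of follow-up".
- Section 2.4, item 10, measures the depression, anxiety, stress and visceral-sensitivity scales at three times, the first being the start of treatment.

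**The concern.** A patient's score after treatment usually depends in part on the score before it. A comparison of final values leaves that predictable part in the error term. A comparison of changes subtracts the whole baseline value, which over-corrects unless the correlation is high. Adjustment by regression uses the baseline to the extent that it predicts the outcome, and does at least as well as either apart from the one degree of freedom it costs. With 30 patients per arm, or about 24 after the 20% dropout assumed in section 2.5, the difference can matter.

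Two further choices are left to the data or to the analyst. The distribution decides whether an outcome is compared on means or on ranks, so the reported effect measure is not fixed in advance. Whether final values or changes are tested also stays open, and the two can differ considerably in power. The trial calls itself a pilot meant to inform larger trials, and for that purpose an adjusted mean difference with a confidence interval is the useful product. A rank test does not give one.

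**Working it through.** **1. The plan's own figure.** Section 2.5 assumes 70% against 30% response, two-sided alpha 0.05, 80% power and 20% dropout. With pooled variance and no continuity correction:

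n = [1.96·√(2·0.5·0.5) + 0.842·√(0.7·0.3 + 0.3·0.7)]² / 0.4² = (1.386 + 0.545)² / 0.16 = 23.3, so 24 per arm.

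24 / 0.8 = 30 per arm, 60 in total. The stated figure reproduces. It rests on the binary responder outcome, so nothing below changes it.

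**2. Inputs for continuous outcomes.** From the article: 30 per arm, 1:1 allocation, two-sided alpha 0.05. Assumed, because the article gives no SD, effect size or correlation for any scale: a true difference of 0.5 SD, equal variances at baseline and follow-up, and a baseline-to-follow-up correlation r of 0.3, 0.5 or 0.7.

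**3. Variance of each analysis, in units of SD².**

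- Final value: 1
- Change from baseline: 2(1 − r)
- ANCOVA: 1 − r²

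**4. Power.** Noncentral t, with noncentrality 0.5 / √(V·2/n) and 2n − 2 degrees of freedom (one fewer for ANCOVA). At n = 30 and r = 0.5, for example:

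- Final value: 0.5 / √(2/30) = 1.94, power 47.8%.
- ANCOVA: 0.5 / √(0.75·2/30) = 2.24, power 59.4%.

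| n per arm | r | t-test, final value | t-test, change | ANCOVA |
|---|---|---|---|---|
| 30 | 0.3 | 47.8% | 36.3% | 51.4% |
| 30 | 0.5 | 47.8% | 47.8% | 59.4% |
| 30 | 0.7 | 47.8% | 69.1% | 76.0% |
| 24 | 0.3 | 39.6% | 29.9% | 42.7% |
| 24 | 0.5 | 39.6% | 39.6% | 49.9% |
| 24 | 0.7 | 39.6% | 59.1% | 66.0% |

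With 30 per arm, ANCOVA gains 3.6, 11.6 and 28.2 points over the final-value test, and 15.1, 11.6 and 6.9 points over the change test.

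**5. The same gain in other terms.** A final-value t-test would need 30 / (1 − r²) per arm to match the variance of ANCOVA with 30: about 33, 40 and 59. The smallest difference detectable with 80% power and 30 per arm falls from 0.736 SD to 0.702, 0.637 and 0.525 SD.

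**6. Does choosing the test by normality inflate false positives?** A simulation with 30 per arm used a Shapiro–Wilk pre-test (an assumption, as the article names no normality test) on normal, lognormal and Poisson data. Type I error was 4.5% to 5.0%. There is no inflation to report.

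**The case against.** The strongest reply is that unadjusted tests are valid in a 1:1 randomised trial, that the outcomes concerned are secondary, and that an article condenses a fuller protocol. All three statements are true. They make this a matter of efficiency, not an error. They do not remove the point, because section 2.9 states a method. An analysis plan that used ANCOVA as the main analysis would depart from that sentence, so the wording needs changing either way.

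A second reply is that the reference to advanced methods leaves room for other models. It does, but the only one named is a logistic model, which serves binary data, and it carries no stated baseline term.

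A reader might infer more than the article supports:

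- *That baseline values are ignored.* A test on change would use them, and section 2.9 does not exclude it. Baseline also defines the responder outcomes. What can be said is that baseline is not used as a covariate.
- *That every continuous outcome loses power.* The Likert global assessment starts at mid-treatment, and time to first SBM or CSBM runs from the first session. Neither has a baseline to adjust for. Elsewhere the loss depends on r. Against final values it is only about 4 points at r = 0.3, and against change scores it shrinks as r rises (about 3 points at r = 0.8, 85.3% against 88.7%).
- *That each visit is tested in isolation.* The text does not say so.
- *That one scale would often switch between t-test and rank test across visits.* This is possible under the rule, but any rate depends on a normality test, a skewness and a correlation between visits that the article does not give.

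The correlation may also be low for CSBM counts, because eligibility requires fewer than three per week and so narrows the baseline range.

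**Conclusion.** The point holds as an improvement to the analysis of secondary continuous outcomes that have a pre-treatment value. The stated tests are valid. They are less precise than adjustment for baselines that the trial already collects, and the plan leaves open both the quantity tested and the scale of comparison.

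Among the three analyses, ANCOVA has the highest power in every row of the table. Its margin over the better of the two t-tests is about 4 to 12 points with 30 per arm, and its margin over the worse one is about 12 to 28 points. These sizes rest on an assumed 0.5 SD difference, assumed r from 0.3 to 0.7 and equal variances. The article cannot show where in that range any given scale lies. The binary primary outcome, the total of 60 patients and the type I error rate are not in question.

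**What to change.** In section 2.9, replace the between-group sentence for each continuous outcome that has a pre-treatment value:

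- Name ANCOVA as the main between-arm analysis, or a linear mixed model with arm, visit, arm-by-visit and the baseline value of the same outcome. Use it whatever the shape of the data.
- Report the adjusted EA-minus-sham difference with its 95% confidence interval at end of treatment and end of follow-up.
- For weekly SBM and CSBM counts, use the screening-diary value as the covariate and robust standard errors.
- If a mixed model is chosen, fit it to the observed data. State that the last-observation-carried-forward rule in section 2.9 does not apply to it.
- Keep the Mann–Whitney test as a sensitivity analysis.

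Outcomes without a baseline, such as the Likert global assessment, keep an unadjusted comparison.

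The cost is a wording amendment, which section 2.10 sends to the IRB for approval before use. It needs no extra patients, visits or data. Section 2.6 keeps the study blinded until the final analysis, so the model can still be fixed before any result is known.
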